## Abstract

**Background:**

Adherence to medication is often low. Pharmacists may improve adherence, but a one-size-fits-all approach will not work: different patients have different needs. Goal of the current study is to assess the effectiveness of a patient-tailored, telephone-based intervention by a pharmacist at the start of pharmacotherapy aimed at improving medication adherence, satisfaction with information and counselling and the beliefs about medicines.

**Methods/Design:**

A cluster randomized controlled intervention trial in 30 Dutch pharmacies, randomly assigned to 1 of 2 intervention groups. Each group consists of an intervention arm and an usual care arm. The intervention arm in the first group is the usual care arm in the second group and vice versa. One intervention arm focuses on patients starting with antidepressants or bisphosphonates and the other on antilipaemic drugs or renin angiotensin system (RAS)-inhibitors. The intervention consists of a telephone call by a pharmacist 2 or 3 weeks after a new prescription. A random sample of pharmacies will send questionnaires 3 months after the first prescription. This contains socio-demographic questions, a measure of beliefs about medicines (BMQ), satisfaction with information received (SIMS, abbreviated) and frequency of pharmacy counselling (Consumer Quality Index, CQI, abbreviated). The primary outcome measure will be medication adherence calculated from dispensing records retrieved 12 months after the intervention. Patients’ beliefs on medication, perception of the quality of information received and pharmacy counselling are secondary outcomes.

**Discussion:**

The TelCIP study will determine the effectiveness of telephone counselling to improve adherence in patients initiating a new treatment. By measuring satisfaction with information and counselling and beliefs about medication the study will also give clues for the reason of a potential increase in adherence. Finally the study will provide information on which patients are most likely to benefit from this intervention.

**Trial registration:**

The trial is registered at http://www.trialregister.nl under the identifier NTR3237.

## Background

Adherence to medication therapy in general is often low [1-3]. Non-adherence to long-term therapies severely compromises the effectiveness of treatment and is therefore critical from both the perspective of quality of life of individual patients and from the perspective of public health and health economics. There are many different factors involved in non-adherence including social and economic factors, the characteristics of the disease and its therapy and health-care provide related factors and patient-related factors such as beliefs about medicines [3-6]. Urquhart et al. and more recently Vrijens et al. argued that three phases of chronic drug treatment can be identified: acceptance of the treatment plan, implementation of the drug regimen and eventually complete discontinuation (non-persistence) of treatment [7,8]. Non-adherence can take place in these three different stages [8].

Non-adherence cannot be regarded as an isolated problem of the patient. The health care provider has to support patients to improve adherence. Patients need information about their medicines to facilitate their appropriate use and understanding of the benefits and risks [5,9,10]. Providing patients with appropriate information about medication has been associated with improved adherence resulting in improved treatment outcomes. In contrast, information not addressing patients’ needs may produce opposite effects [11,12]. A great part of the information provided by the healthcare practitioner is forgotten or remembered incorrectly [13,14]. Therefore it would be desirable to consider repeated opportunities for providing information [15]. But providing information alone is not enough: patients need to be motivated and be involved in decision making [16]. Negative attitudes and barriers that prevent adherent behaviour should be addressed.

Different interventions have been studied to improve adherence. Multidisciplinary and multifactorial interventions were more effective than single focus-interventions.

Ideally interventions should focus on practical and perceptual barriers that affect adherence. Practical barriers may include complex dosage regimens, the size of tablets, the cost of prescriptions, the route of delivery (e.g. rectal or oral) and side effects. In contrast, perceptual barriers are more complex and are based on an internal negotiation between the perceived necessity of the treatment and any concerns relating to it. Interpersonal communication provides opportunity to tailor information to the practical and perceptual barriers of a specific patient [17,18].

Pharmacists can play an important role in improving adherence: they are easily accessible health-care providers, have frequent contacts with patients, have extensive knowledge about drug therapy and are equipped to provide information and monitor patients’ experiences and adherence at visit to the pharmacy. However, it is not always possible to tailor counselling to patient needs [10]. Some patients are unable to visit the pharmacy. Others perceive a lack of privacy in the pharmacy or do not have time for counselling at the moment of the visit. Sometimes patients are already overwhelmed by information provided by other health care providers and therefore not open to receive additional information from the pharmacy.

A different approach might improve patient counselling. Counselling by telephone has proven to be an effective, easy implementable alternative [19,20]. Although it has some disadvantages like the lack of non-verbal communication, it can resolve some of the barriers mentioned above. The patient is counselled in his or her own safe environment and lack of privacy is not an issue. From the health care providers’ perspective: it is easier to implement since the calls can be scheduled. Competent employees can be appointed and can better anticipate on the subject.

Given the above we designed an intervention aimed at preventing patients initiating treatment from becoming non-adherent. We will focus on patient starting with lipid modifying agents, Renin-Angiotensin-System (RAS)-inhibitors, antidepressants or bisphosphonates. We choose these medications because (1) they are intended for long-term use, (2) are prescribed frequently enough to enable the inclusion of a sufficient number of patients during the study period, (3) adherence is often low and (4) the characteristics of patients using antidepressants, bisphosphonates or RAS-inhibitors/lipid lowering drugs are different and patients might weigh risks and benefits of these four groups of medicines differently.

The main objective of the study is to assess the effectiveness of a patient-tailored, telephone intervention by a pharmacist at the start of pharmacotherapy on (1) adherence, (2) beliefs about medicines and (3) satisfaction with information and counselling. We also will assess to what extent counselling by telephone fulfils patients’ needs.

## Methods and design

### Study design

We will conduct a multicentre community pharmacy-based, cluster randomized controlled trial (CRT) (Figure 1). Pharmacies are alternately assigned to either group A or group B in a 1:1 ratio. Given the nature of the study design it is impossible for both the researchers and the pharmacists to be blinded to the group assignment. Each group consists of an intervention (TelCIP) arm and a usual care arm. The TelCIP arm in group A focuses on the same medication as the usual care arm in group B and vice versa.

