**Figure 1 F1:**
[figure not shown]
**Study design.** Pharmacies are randomized in two groups. Each group consists of an intervention (TelCIP) arm and a usual care arm. The TelCIP arm in group A focuses on the same medication as the usual care arm in group B and vice versa.

We performed a pilot in three pharmacies in the period of October 2010 to December 2010. In this pilot we tested the manuals, the feasibility, the software to select the patients (queries) and the online registration form. This pilot led to some practical adjustments in the manuals, the software and the online registration form. The design and the intervention proved to be feasible.

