### Recruitment of pharmacies

Independent pharmacies franchisees of ‘Service Apotheek’ are invited to participate in the study. The study design is presented at 4 regional meetings for pharmacies where they could apply for participation. In a weekly newsletter pharmacies are also invited to participate in the study. The pharmacies are periodically visited by staff of the franchise formula and during these visits; the study is also brought to the attention of the pharmacist. Participating health care providers have to follow an e-learning communication training based on the Health Belief Model. The Health Belief Model (HBM) suggests that adherence behaviour is influenced by perceived severity (beliefs about how severe the condition is), perceived susceptibility (the extent to which the patient feels at risk of suffering from the condition) and the effects and disadvantages of the advised behaviour [21,22]. The course aims to train pharmacists and technicians to understand the opinions and behaviour of patients (related to medication intake). Furthermore the training aims to familiarize pharmacists with the concept of concordance. The course also pays attention to sources for information for patients, possibilities and limitations of package leaflet and the package labels. The course takes about three hours, includes case studies and a concluding test to assess the level of theoretical knowledge on communication and concordance.

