### Sample size

Power calculation is focused on the primary outcome, the proportion of adherent patients. With a type one error (α) for a two sided test of 0.05 and a probability of rejecting the null hypothesis of 0.80 (1-β) 294 patients per arm are needed for demonstrating an improvement of the proportion of adherent patients from 70% to 80% [32]. For cluster randomisation a correction is needed based on the Intraclass correlation coefficient (ICC). When using ICC = 0.02 we need at least 15 pharmacies to include at least 30 patients per group of medication for the intervention (4), so 15*30*4 = 1800 patients in the intervention arms and 1800 in the usual care arms. We expect an average response rate of 30% on the questionnaires and with the aim to receive at least 100 responses per arm, we estimated to invite at least 670 patients to participate in the survey.

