### Limitations

The cluster randomized design of the study may compromises the internal validity of the study since difference at baseline between the levels of the provided care between pharmacies cannot be ruled out. It is likely that a part of the patients in the intervention groups will not be available for the intervention, because contact details are lacking or patients cannot be reached. Since in the control group these patients cannot be excluded this can cause a selection bias in the per-protocol analysis.

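### The Methods say pharmacies are assigned alternately, while the abstract, the Figure 1 legend and the Methods' own design label say randomised; the statements conflict and nothing printed reconciles them

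*Protocol article*

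**What the plan says.** The protocol article describes the allocation of pharmacies in several places.

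- Abstract, Methods/Design: "A cluster randomized controlled intervention trial in 30 Dutch pharmacies, randomly assigned to 1 of 2 intervention groups".
- Study design, first sentence: the study is labelled a cluster randomised controlled trial.
- Study design, next sentence: "Pharmacies are alternately assigned to either group A or group B in a 1:1 ratio".
- Figure 1 legend: "Pharmacies are randomized in two groups".
- Limitations: "The cluster randomized design of the study may compromises the internal validity of the study", because differences between pharmacies in the level of care at baseline cannot be ruled out. Alternation is not mentioned there.

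Two further statements bear on the consequences. Study design adds that "it is impossible for both the researchers and the pharmacists to be blinded to the group assignment". Recruitment of pharmacies says "The study design is presented at 4 regional meetings for pharmacies where they could apply for participation", and that pharmacies were also invited by newsletter and during visits by franchise staff.

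**The concern.** The only sentence that says how pharmacies are placed in a group names a deterministic method. Every other description uses the language of randomisation. Both cannot be right as printed. This is more than detail left out of a condensed article, because the detail that is given contradicts the label.

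Two things are at stake. The first is what the trial may claim: a study allocated by strict alternation is quasi-randomised, and readers would wrongly appraise it as randomised. The second is freedom from bias in the comparisons within a drug class. For antidepressants and bisphosphonates, group A pharmacies deliver the call and group B pharmacies give usual care. For RAS-inhibitors and lipid-lowering drugs the roles are reversed. Each of these comparisons is between two sets of pharmacies, and random allocation is what would make the sets comparable in expectation. The article wants to learn which medication groups benefit most, so these comparisons matter.

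**Working it through.** **The plan's own figure.** The sample size does not depend on the allocation method, but it supplies inputs used below. From Sample size: 70% against 80% adherent, two-sided alpha 0.05, power 0.80.

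n = [1.96 × √(2 × 0.75 × 0.25) + 0.8416 × √(0.70 × 0.30 + 0.80 × 0.20)]² / 0.10² = (1.2002 + 0.5119)² / 0.01 = 293.1, so 294 per arm, as stated.

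With ICC 0.02 and 30 patients per pharmacy the design effect is 1 + 29 × 0.02 = 1.58. The planned 15 × 30 = 450 per arm gives about 79% power. Nothing here changes.

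**The statements side by side.** Alternation fixes each assignment from the one before, and randomisation does not. They could be reconciled if the article mentioned alternation down a randomly ordered list, or a balanced random draw described loosely. It mentions neither.

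**What literal alternation would imply (30 pharmacies, 1:1).**

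- Possible sequences: 2 (ABAB… or BABA…), against C(30,15) = 155,117,520 for random 15:15 allocation.
- Share of assignments that can be guessed, with a random first assignment and the running sequence visible: (0.5 + 29)/30 = 98%.
- For comparison, permuted blocks of 4 under the best guessing strategy: (1/2 + 2/3 + 2/3 + 1)/4 = 71%.

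**Which estimates would be exposed.** Let q be a general difference in quality of care, group A minus group B, on the adherence scale.

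- Antidepressants and bisphosphonates (A minus B): true effect + q.
- RAS-inhibitors and lipid-lowering drugs (B minus A): true effect − q.
- Equal-weight average over the two pairs: q cancels, provided it is the same for both pairs.

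The class-specific estimates carry the bias in opposite directions, and the pooled one largely does not.

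**Illustrative scale only.** At the mid-range proportion 0.75, the between-pharmacy SD is √(0.02 × 0.75 × 0.25) = 0.061. Assume that k of 15 pharmacies in one group lie 1 SD above average and k of 15 in the other lie 1 SD below. The shift in a class-specific difference is then 2 × (k/15) × 0.061:

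| k | Shift, percentage points |
|---|---|
| 0 | 0 |
| 1 | 0.8 |
| 3 | 2.4 |
| 5 | 4.1 |

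Both k and the 1 SD displacement are assumptions with no source in the article. For scale, the chance imbalance between two properly randomised groups of 15 pharmacies has SD 0.061 × √(2/15) = 0.022, or 2.2 points.

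**The case against.** The strongest reply is that this is loose wording. The abstract, the design label and the figure legend all say randomised, and one sentence says alternately. That sentence may mean only that the groups were kept balanced 1:1, or that a randomly ordered list was split in turn. This stands as a possibility, and it is why the finding is a contradiction to resolve and not proof that the allocation was non-random. It does not remove the contradiction.

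A reader might go further and infer that pharmacies joined one at a time, that recruiters knew the next assignment, and that allocation was therefore fully predictable. The article does not support this. It gives the routes of invitation, but not the order of entry, who controlled it, or whether allocation waited until all pharmacies had enrolled. The blinding sentence names researchers and pharmacists and concerns knowledge of the assignment; it does not say who could see the next one.

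The crossed design is also a fair defence. Every pharmacy delivers the intervention for one pair of drug classes and usual care for the other, so no pharmacy is a pure control and there is less reason to steer. That weakens the incentive without removing it, and the class-specific comparisons remain between pharmacies.

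Finally, the planned multilevel model and the second analysis of confounding might be thought to cover the problem. The multilevel model accounts for clustering, not for a systematic difference between the two groups. The confounding analysis does not name pharmacy-level prior adherence.

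**Conclusion.** The contradiction is certain. Either the allocation sentence or the label randomised is wrong as written, and the documents do not show which.

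The consequences are conditional. If alternation was used, the label must go, and the class-specific comparisons lack the protection of randomisation. Foreseeing assignments would further require sequential entry and a visible running sequence, neither of which is documented. Comparisons pooled over the two drug-class pairs are much less exposed, assuming the quality difference is similar for both pairs.

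A reader might take the 2.4-point line of the table as an estimate of bias, about a quarter of the planned 10-point effect. It is not one. It rests on an assumed steering scenario and is about the size of one SD of ordinary chance imbalance between pharmacies. A correct standard error covers chance imbalance but not bias; even so, nothing in the article shows that steering took place.

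**What to change.** The change depends on what was or will be done.

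1. **Pharmacies not yet allocated:** replace the alternation sentence with a computer-generated 1:1 random list, concealed from those who recruit and released for each pharmacy only after it has committed. Preparing the list costs very little.
2. **Allocation was in fact random:** correct the Study design sentence and state how the sequence was generated and concealed. This is a text change only.
3. **Pharmacies were already alternated:** change the randomisation wording in the abstract, Study design and the Figure 1 legend to quasi-randomised (alternate allocation), make the matching wording in Sample size and Limitations consistent, and name alternation in Limitations as a threat to the class-specific comparisons. The price is a weaker design claim.

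In the third case a sensitivity analysis could optionally adjust for each pharmacy's earlier class-specific proportion adherent, taken from its own dispensing records. That costs one extra historical query per pharmacy. It supports the interpretation but does not replace correcting the text. If a bias figure is reported, present it as an assumption with a range.

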**Figure 1 F1:**
[figure not shown]
**Study design.** Pharmacies are randomized in two groups. Each group consists of an intervention (TelCIP) arm and a usual care arm. The TelCIP arm in group A focuses on the same medication as the usual care arm in group B and vice versa.

We performed a pilot in three pharmacies in the period of October 2010 to December 2010. In this pilot we tested the manuals, the feasibility, the software to select the patients (queries) and the online registration form. This pilot led to some practical adjustments in the manuals, the software and the online registration form. The design and the intervention proved to be feasible.

### Recruitment of pharmacies

Independent pharmacies franchisees of ‘Service Apotheek’ are invited to participate in the study. The study design is presented at 4 regional meetings for pharmacies where they could apply for participation. In a weekly newsletter pharmacies are also invited to participate in the study. The pharmacies are periodically visited by staff of the franchise formula and during these visits; the study is also brought to the attention of the pharmacist. Participating health care providers have to follow an e-learning communication training based on the Health Belief Model. The Health Belief Model (HBM) suggests that adherence behaviour is influenced by perceived severity (beliefs about how severe the condition is), perceived susceptibility (the extent to which the patient feels at risk of suffering from the condition) and the effects and disadvantages of the advised behaviour [21,22]. The course aims to train pharmacists and technicians to understand the opinions and behaviour of patients (related to medication intake). Furthermore the training aims to familiarize pharmacists with the concept of concordance. The course also pays attention to sources for information for patients, possibilities and limitations of package leaflet and the package labels. The course takes about three hours, includes case studies and a concluding test to assess the level of theoretical knowledge on communication and concordance.

### Recruitment of patients

Patients starting with treatment will be recruited from 30 community pharmacies in different areas of The Netherlands in the period between May 2011 and March 2013.

Patients in the intervention arm will be selected through an automated selection procedure and presented to the pharmacist. This selection is based on dispensing data and most inclusion and exclusion criteria are incorporated. The same selection will be used to include patients in the usual care group. However not all exclusion criteria can be incorporated in the automated selection and after selection, pharmacist can decide not to include a patient. We will ask the pharmacist to register the reason. However due to the study design the possibility of introducing a selection bias exists, and therefore our primary analysis will be based on the intention-to-treat principle (ITT). Patients will be included in the analysis if they are eligible according to selection criteria based on the pharmacy data. In a per-protocol (PP) analysis we will compare the patients who actually received counselling with patient who received usual care.

#### Inclusion criteria

• Receiving medication for a chronic condition for the first time in 12 months:

• Intervention arm A: starting with an antidepressant or bisphosphonate

• Intervention arm B: starting with a Renin-Angiotensin-System (RAS)-inhibitor or lipid-lowering drug.

#### Exclusion criteria

• Under 18 years of age

• Not responsible for their own medication intake

• Receiving their medication weekly in a multidose dispensing system or multi-compartment dispensing system (e.g. Baxter system or ‘pill organiser’)

• Switching to other medication within the ATC3-group in the 12 months before inclusion

• Receiving medication for a short term indication (e.g. antidepressant for smoking cessation)

• Patients not speaking Dutch nor another language spoken fluently by the healthcare provider

• Patients starting in the same week with both a medication from intervention arm A (antidepressant or bisphosphonate) and a medication from arm B (RAS-inhibitor or lipid-lowering drug).

• Patients without access to a telephone.

Patients in the TelCIP-arms meeting all eligibility criteria receive an information letter, are invited for the study participation and asked for informed consent.

